### Eligibility Criteria and Recruitment

All of the following inclusion criteria must be met to participate in this study: dyspnea unexplainable by other diseases (heart failure, renal failure, etc), diagnosis with SARS-CoV-2 infection through polymerase chain reaction or loop-mediated isothermal amplification within 1 week, at least one lung opacity on imaging suggestive of consolidation, P/F ratio of 300 or below or an SpO2 of 93% or below (indoor air), being hospitalized, requiring supplemental oxygen, requiring nasal high-flow oxygen therapy or noninvasive mechanical ventilation or requiring invasive mechanical ventilation, 16 years or older at the time of consent, and written consent. Consent is obtained from patients with pneumonia who are hospitalized for COVID-19 and who may meet the eligibility criteria.

Consent is obtained in writing from the individual. Informed consent will be obtained from a representative of the patient if the patient is a minor or objectively judged to have insufficient understanding of the subject due to a serious illness. The representative will be selected from the patient’s spouse, parents, siblings, children/grandchildren, grandparents, relatives living in the same household, or close relatives of the patient.

The following tests, observations, and evaluation will be performed as part of the screening test: vital information (date of birth, gender, height, weight, presence of oxygen therapy); clinical history (onset: date of onset, symptoms), treatment history (type, treatment period of therapeutic drugs/therapy), medical history, complications, allergies, date of admission, date of polymerase chain reaction positive result, concomitant drug confirmation (medication currently being taken by the patient shall be confirmed at the time of the screening), vital signs, blood test (hematological test, blood biochemical test), urinalysis, and imaging test (presence of pneumonia complications).

As a result of the screening, if the patient meets the enrollment criteria stated in the eligibility criteria, they will be enrolled to the study, and PMX-DHP will commence. Otherwise, the patient fails the screening and will no longer participate in the study.

The following exclusion criteria will be used: severe progression of multiple organ failure; P/F ratio of 100 or below; extracorporeal membrane oxygenation (ECMO); hospitalization for more than 15 days; platelet count of 20,000/μL or less; cytotoxic or biological treatments (anti-interleukin [IL]–1, anti-IL-6 [tocilizumab or sarilumab], T cell or B cell targeted treatment [rituximab, etc], tyrosine kinase inhibitor or interferon) within 4 weeks prior to consent; treatment with tumor necrosis factor inhibitor within 2 weeks prior to consent; treatment with convalescent plasma or intravenous immunoglobulin for COVID-19; and consideration by the principal investigator or subinvestigator to be unfit to participate in this study.

In case of nonparticipation in the study, administration of remdesivir, dexamethasone, and tocilizumab will be considered if indicated and not already administered. Furthermore, systemic management including oxygen therapy will be performed for deterioration of respiratory function.

A schematic illustration of the study design is presented in Figure S1 in Multimedia Appendix 1.

### Sample Size Estimation

In this study, the efficacy of PMX-DHP will be evaluated by comparing the improvement rate (decrease) of 1 point or more from status 4, 5, or 6 on day 15 based on the eight-category evaluation with the COVID-19 registry. In a paper that reported on the compassionate use of remdisivir for COVID-19 cases [23], of 51 cases who were under invasive ventilation, noninvasive oxygen support, or low flow oxygen (corresponds to the status 4, 5, and 6 in this study), improvement by at least 1 stage was noted in 34 cases (approximately 57%; median follow-up period: 18 days). Further, in a randomized clinical trial investigating the effect of lopinavir-ritonivar on COVID-19 about 38% (75/199) of cases recovered (improved by 2 points or more on a 6-point scale) 14 days after randomization [24]. Based on the aforementioned, we assume that approximately 50% to 60% of non–PMX-DHP COVID-19 cases will improve by 1 point. On the other hand, although there is insufficient data on the expected effects of PMX-DHP, we can consider PMX-DHP effective if the improvement rate of cases in this study is 1.5 times that of the non–PMX-DHP cases.

We set a 2-sided type I error at 10%. When the improvement rate of non–PMX-DHP cases is approximately 55%; if there are 30 cases in this study; and the control group is set at 30, 60, and 90 cases, the detection power would be approximately 65%, 78%, and 83%, respectively. Similarly, if the improvement rate of non–PMX-DHP cases is approximately 50%, the detection power would be 54%, 67%, and 72%, respectively. If the improvement rate is approximately 60%, the detection power would be 78%, 90%, and 94%, respectively. However, when compared with control cases, the detection power fluctuates due to the adjustment in the confounding factor.

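### The protocol gives 34 of 51 improved cases as about 57%, but 34/51 is 66.7%; if the counts are right, the only cited 1-point improvement rate lies above every control rate for which power was calculated

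*Protocol article*

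**What the plan says.** All the figures are in the protocol article, Methods, Sample Size Estimation.

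- **First source:** a compassionate-use remdesivir report. The relevant subset is described as "of 51 cases who were under invasive ventilation, noninvasive oxygen support, or low flow oxygen", matched by the protocol to status 4, 5 and 6. The result is given as "improvement by at least 1 stage was noted in 34 cases (approximately 57%; median follow-up period: 18 days".
- **Second source:** a randomized trial of lopinavir-ritonavir, in which "about 38% (75/199) of cases recovered (improved by 2 points or more on a 6-point scale) 14 days after randomization".
- **Control rate:** "Based on the aforementioned, we assume that approximately 50% to 60% of non–PMX-DHP COVID-19 cases will improve by 1 point".
- **Effect:** "we can consider PMX-DHP effective if the improvement rate of cases in this study is 1.5 times that of the non–PMX-DHP cases".
- **Sample sizes and alpha:** 30 PMX-DHP cases against 30, 60 or 90 controls, two-sided type I error 10%.
- **Stated power (30/60/90 controls):** 54/67/72% at a control rate of 50%, 65/78/83% at 55%, and 78/90/94% at 60%.

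The Statistical Analysis section describes the efficacy comparison as a propensity-score analysis against the registry at a two-sided 5% level. It sets no 1.5-fold threshold.

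**The concern.** The numerator, denominator and percentage of the first source stand in one sentence and do not agree. The slip matters because of where it sits. The printed 57% falls inside the assumed 50% to 60% range, whereas the rate given by the printed counts falls outside it. The second source cannot fill the gap: it counts improvement of 2 points or more on a 6-point scale, which is stricter than the 1-point improvement used here.

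The effect is also fixed as a ratio. A ratio of 1.5 is attainable at 50% to 60% but reaches its ceiling at two-thirds, exactly the rate that 34/51 gives. If registry controls improve at about that rate, the planned effect has no attainable counterpart, and the protocol gives no power figure that applies.

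**Working it through.** **1. The percentage**

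- 34/51 = 0.667. The exact (Clopper-Pearson) 95% CI is 52% to 79%.
- 57% of 51 is 29.1 cases. The pairs that would give about 57% are 29/51 = 56.9% and 34/60 = 56.7%.
- For comparison, 75/199 = 37.7%, which agrees with the stated 38%.

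**2. Reproducing the stated powers**

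The article does not name its formula. A two-proportion normal approximation with continuity correction fits:

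power = Φ{ [ |p1 − p0| − c − 1.645·s0 ] / s1 }

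Here p0 is the control rate with n0 controls, and p1 is the PMX-DHP rate with n1 = 30. The other terms are c = 0.5(1/n0 + 1/n1), s0 = √[p̄(1 − p̄)(1/n0 + 1/n1)] with p̄ the pooled rate, and s1 = √[p0(1 − p0)/n0 + p1(1 − p1)/n1]. The value 1.645 corresponds to two-sided 10%.

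| p0 | p1 = 1.5·p0 | Computed, 30/60/90 controls | Stated |
|---|---|---|---|
| 50% | 75% | 53.6 / 66.6 / 72.1% | 54 / 67 / 72% |
| 55% | 82.5% | 65.3 / 78.2 / 83.4% | 65 / 78 / 83% |
| 60% | 90% | 78.5 / 89.8 / 93.7% | 78 / 90 / 94% |

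All nine agree within 1 point, so the power arithmetic is sound for its inputs and the formula can be used for the corrected case.

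**3. The planned effect at the rate the counts give**

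1.5 × 66.7% = 100%. All 30 of 30 PMX-DHP patients would have to improve. Above 66.7% a ratio of 1.5 is impossible.

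**4. Power at a 66.7% control rate**

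The PMX-DHP rates are taken from the plan's own scenarios: 82.5% (from the 55% scenario) and 90% (from the 60% scenario, the highest rate the plan implies).

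| p1 | n0 | p1 − p0 | c | s0 | s1 | Argument of Φ | Power |
|---|---|---|---|---|---|---|---|
| 82.5% | 30 | 0.1583 | 0.0333 | 0.1124 | 0.1105 | −0.542 | 29.4% |
| 82.5% | 60 | 0.1583 | 0.0250 | 0.1005 | 0.0923 | −0.346 | 36.5% |
| 82.5% | 90 | 0.1583 | 0.0222 | 0.0960 | 0.0853 | −0.256 | 39.9% |
| 90% | 30 | 0.2333 | 0.0333 | 0.1064 | 0.1020 | 0.245 | 59.7% |
| 90% | 60 | 0.2333 | 0.0250 | 0.0975 | 0.0819 | 0.585 | 72.1% |
| 90% | 90 | 0.2333 | 0.0222 | 0.0941 | 0.0740 | 0.761 | 77.7% |

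At 82.5% without the continuity correction, the powers would be about 41%, 47% and 50%, still well below the stated 65%, 78% and 83%. The 10% level of the sample-size section is kept throughout, so that the change shown comes from the control rate alone.

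**The case against.** The strongest reply is that the planning range may be right and a count misprinted. Both 29/51 and 34/60 give about 57%, and 57% is the value that fits the assumed range. The cited report cannot be consulted here. This stands: everything that follows from 66.7% is conditional on the counts.

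Second, the control range was a judgement drawn from two sources, not a copy of one number. The first source also has a median follow-up of 18 days rather than a day-15 assessment, and the controls here will be selected registry patients. This stands too. The interval of 52% to 79% includes 55% and 60%, so 66.7% is not shown to be the day-15 control rate. It remains true that the first source is the only one cited for a 1-point improvement.

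Third, a reader might infer from "effective if the improvement rate of cases in this study is 1.5 times" that the trial could not succeed if controls improve at two-thirds. The document does not support that. The sentence stands in the sample-size section and supplies the effect used for power. The Statistical Analysis section judges efficacy by the propensity-score comparison and sets no 1.5-fold threshold, so a significant result with a smaller ratio is possible. What remains is a wording problem: the sentence reads like a success criterion and should be clarified.

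Fourth, a reader might conclude that the stated powers are miscalculated. They are not; all nine reproduce.

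**Conclusion.** Wrong as written. The sentence contradicts itself: 34 of 51 is 66.7%, not about 57%, and at least one of 34, 51 and 57% must be wrong. That much rests on no assumption.

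The consequence for the design is conditional. If the counts are right, the closest cited rate lies about 7 percentage points above the highest control rate considered (66.7% against 60%), and the 1.5-fold effect becomes 100% improvement. Power for a PMX-DHP rate of 82.5% then falls to 29.4%, 36.5% and 39.9%, from the 65%, 78% and 83% stated for that same PMX-DHP rate against 55% controls. At 90% it would be 59.7%, 72.1% and 77.7%. These figures assume an unadjusted comparison at two-sided 10% and a registry rate equal to 66.7% at day 15, which the 18-day median follow-up does not establish. If instead a count is the misprint, the planning range stands and only the count needs correcting.

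**What to change.** 1. Check the numerator, denominator and percentage against the cited report and correct whichever is wrong.
2. If 34/51 stands, add power scenarios at control rates of 65% to 70%. Pair each with an attainable PMX-DHP rate, because the 1.5 ratio cannot be carried above 66.7%. Report the less favourable powers beside the existing ones.
3. State in Sample Size Estimation that the 1.5-fold ratio is the effect assumed for planning, and that efficacy is judged by the propensity-score comparison in Statistical Analysis, with its confidence interval.

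The cost is one source check, a short recalculation and some rewording. The stated power becomes less favourable if the counts hold. No extra patients are needed.

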### Statistical Analysis

The main purpose of this study is to verify the efficacy in PMX-DHP cases compared to the control in the COVID-19 registry for the primary end point. Particularly, the efficacy of PMX-DHP will be evaluated by comparing the improvement rate (decrease) of 1 point or more from status 4, 5, or 6 on day 15 based on the eight-category evaluation with the COVID-19 registry.

Not hospitalized with resumption of normal activitiesNot hospitalized but unable to resume normal activitiesHospitalized not requiring supplemental oxygenHospitalized requiring supplemental oxygenHospitalized requiring nasal high-flow oxygen therapy, noninvasive mechanical ventilation, or bothRequiring invasive mechanical ventilationRequiring ECMODeath

The status and the percentage of PMX-DHP cases at each evaluation time will be calculated, and the number and percentage of people whose day 15 status improved by 1 or more points from day 1 will be calculated. Furthermore, the following analysis will be planned for comparison with control cases.

Bias is included when comparing the rate of improvement of control cases for 15 days from the time of hospitalization against cases that underwent PMX-DHP several days after hospitalization. Therefore, the number of days from hospitalization to the date of PMX-DHP administration will be calculated for each case.

The effect of PMX-DHP will be estimated using the propensity score based on the data, which integrates this study and the registry. The propensity score will be created based on age, gender, body temperature, etc, and analysis methods such as matching will be used. A significance level on both sides of 5% will be used.

The following results will be calculated for cases enrolled in this study:

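### Power is calculated at a two-sided 10% level, but the same primary comparison is to be tested at two-sided 5%, and nothing in the article reconciles the two

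*Protocol article*

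**What the plan says.** In the protocol article, Sample Size Estimation plans the primary comparison, improvement of at least one category by day 15 against registry patients. It declares "We set a 2-sided type I error at 10" per cent. On the control rate it says "we assume that approximately 50% to 60% of non–PMX-DHP COVID-19 cases will improve by 1 point". On the effect it says "we can consider PMX-DHP effective if the improvement rate of cases in this study is 1.5 times that of the non–PMX-DHP cases". It then tabulates power "if there are 30 cases in this study; and the control group is set at 30, 60, and 90 cases". For a 55% control rate, "the detection power would be approximately 65%, 78%, and 83%, respectively"; for 50% it gives 54, 67 and 72%, and for 60% it gives 78, 90 and 94%. Its one caveat is that adjustment for confounding will move the power.

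Statistical Analysis opens with the same comparison: "The main purpose of this study is to verify the efficacy in PMX-DHP cases compared to the control in the COVID-19 registry for the primary" outcome. Further on it says "The effect of PMX-DHP will be estimated using the propensity score based on the data, which integrates this study and the registry", and the paragraph containing that sentence ends with "A significance level on both sides of 5% will be used". Secondary end points are then to be handled in the same way as the primary one, with propensity scores.

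**The concern.** Two sections of one document give different significance levels for one comparison, and that comparison carries the efficacy claim of a single-group study posited at 30 treated patients. Two things are at stake.

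- **The success criterion is open.** A result with p between 0.05 and 0.10 meets one section's criterion and fails the other's. Unless the level is settled beforehand, it could be chosen after the result is known.
- **The powers describe a different test.** Figures worked out at 10% do not describe what a 5% test will detect. The only caveat offered, on confounding, does not cover a change of level.

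**Working it through.** **Inputs, all from Sample Size Estimation.** Treated n = 30; control n_C = 30, 60 or 90; control rate p_C = 0.50, 0.55 or 0.60; treated rate p_T = 1.5 × p_C = 0.75, 0.825 or 0.90; two-sided level 10%. The 5% level comes from Statistical Analysis.

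**Formula.** The article names no test. The formula that reproduces its figures is the normal approximation for two proportions, with pooled variance under the null, unpooled variance under the alternative, and a continuity correction:

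- Δ = p_T − p_C
- p̄ = (30·p_T + n_C·p_C)/(30 + n_C)
- SE0 = √[p̄(1−p̄)(1/30 + 1/n_C)]
- SE1 = √[p_T(1−p_T)/30 + p_C(1−p_C)/n_C]
- c = ½(1/30 + 1/n_C)
- power = Φ[(Δ − c − z·SE0)/SE1], with z = 1.6449 at 10% and 1.9600 at 5%

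**One cell in full: control rate 55%, 90 controls, stated power 83%.** Δ = 0.275; p̄ = (24.75 + 49.5)/120 = 0.61875; SE0 = 0.10239; SE1 = 0.08696; c = 0.02222.

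- At 10%: (0.27500 − 0.02222 − 0.16842)/0.08696 = 0.970, power 83.4%. This matches the stated 83%.
- At 5%: (0.27500 − 0.02222 − 0.20068)/0.08696 = 0.599, power 72.5%.

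**All nine cells (power in %).**

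| Control rate | Controls | Stated | Corrected, 10% | Corrected, 5% | Uncorrected, 5% |
|---|---|---|---|---|---|
| 50% | 30 | 54 | 53.65 | 40.73 | 51.7 |
| 50% | 60 | 67 | 66.56 | 53.49 | 63.0 |
| 50% | 90 | 72 | 72.13 | 59.48 | 68.2 |
| 55% | 30 | 65 | 65.25 | 52.48 | 63.8 |
| 55% | 60 | 78 | 78.20 | 66.33 | 75.4 |
| 55% | 90 | 83 | 83.40 | 72.54 | 80.4 |
| 60% | 30 | 78 | 78.50 | 67.48 | 78.0 |
| 60% | 60 | 90 | 89.84 | 81.23 | 88.2 |
| 60% | 90 | 94 | 93.73 | 86.85 | 92.1 |

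**Reproduction.** The corrected formula at 10% agrees with every stated figure to about half a point. The uncorrected pooled formula at 10% does not: it gives 64/75/79, 75/85/89 and 87/94/97. An arcsine calculation at 5% comes close but misses two cells by more than 2 points (64.9 against 67; 80.3 against 78). The powers were therefore computed at 10%, as the section says.

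**Size of the change.** With the corrected formula kept and only the level moved, power falls by 6.9 points (60%, 90 controls) to 13.1 points (50%, 60 controls). Six of the nine stated powers reach 70% (72, 78, 83, 78, 90, 94); at 5% three do (72.5, 81.2, 86.9).

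**Dependence on the test.** Without the continuity correction, power at 5% is 0 to 4 points below the stated figures. That gap is small because two changes offset each other: dropping the correction raises power and tightening the level lowers it. Like for like, the uncorrected test also loses 4.5 to 12.7 points between 10% and 5%.

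**The case against.** The best defence has four parts.

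- **The powers are right for the level printed beside them.** This stands. A reader might infer that the sponsor miscalculated; the reproduction shows otherwise. The fault lies between the sections.
- **The 7 to 13 point shortfall rests on an inferred formula.** This also stands. A reader might infer that every stated power must fail at 5%. The article names no test and plans a propensity-score analysis, with matching as one example. Under the uncorrected pooled approximation the shortfall is 0 to 4 points. Exact enumeration of that test puts one cell slightly above its stated value (79.6 against 78, at 60% with 30 controls).
- **No power target is set.** The article posits 30 cases and tabulates the power, and warns that confounder adjustment will alter it. A reader might infer that the trial must enrol more patients, or that a 10% level obliges the sponsor to call it exploratory. The article supports neither inference.
- **An analysis plan not shown may settle the level.** It may choose one, but it cannot make both sentences true of the same comparison. Nor can the 5% be confined to secondary end points: it closes the paragraph on the registry comparison, and the secondary analyses are described as following the primary method.

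**Conclusion.** The inconsistency holds as written: one primary comparison, planned at two-sided 10% and tested at two-sided 5%, with no reconciling text. This part needs no assumption about the test.

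The effect on power is conditional. If the final test behaves like the continuity-corrected one that reproduces the article's figures, the stated powers are about 7 to 13 points too high for a 5% test, and at the middle control rate of 55% no control size reaches 80% (best about 73%, stated 83%). If it behaves like an uncorrected pooled test, they are 0 to 4 points too high. Both results assume independent groups, the article's 1.5-fold rate, and no loss from matching or weighting, which the article mentions but does not quantify.

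**What to change.** State one two-sided significance level for the primary comparison in both Sample Size Estimation and Statistical Analysis, before the data are fixed.

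- **If 5% is meant:** change the level in Sample Size Estimation, name the test behind the power figures and restate all nine. With the continuity-corrected test, for 30/60/90 controls, they become 41/53/59% (control rate 50%), 52/66/73% (55%) and 67/81/87% (60%). With an uncorrected pooled test they become 52/63/68%, 64/75/80% and 78/88/92%.
- **If 10% is meant:** correct the sentence in Statistical Analysis; the nine powers can stay.

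The cost is one sentence and at most nine figures, which become less favourable under 5%, or in one cell at best unchanged to the nearest point. No extra patients are needed.

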### Intervention: Medical Device, Protocol, and Combination Therapy

The medical device used is an adsorptive blood-purifying device (product name Toraymyxin, model PHX-20R, approval 20500BZZ00926000). This blood-purifying device selectively adsorbs and removes blood endotoxin by whole blood hemoperfusion. This product is intended to improve the pathological condition by treating patients with severe pathological conditions associated with endotoxemia or thought to be due to gram-negative bacterial infections.

The appearance of this product is shown in Table 2 and Figure S2 in Multimedia Appendix 2.

**Table 2 table2:** Structure.

	Toraymyxin (model PHX-20R)
Length (mm)	225
Maximum diameter (mm)	63
Body diameter (mm)	49
Blood volume (mL)	135 (±5)

This product is sealed one by one in a sterilized bag and packed in a box. Information about storage, delivery, disposal, potential serious side effects, and caution for concomitant treatment can be obtained at the manufacturer’s website [25]. In general, an adverse event is an undesirable symptom, sign, disease, or abnormal laboratory test value that occurs in a patient regardless of their causal relationship with the study or the pharmaceuticals used in this study. An adverse event occurs after the start of treatment. An adverse event will be considered a serious adverse event if the principal investigator or subinvestigator rules that the following criteria have been met: death or risk of leading to death, events that require hospitalization at a medical institution for treatment or require the extension of hospitalization, impairment or risk of leading to impairment, or congenital diseases or abnormalities that could be inherited by later generations.

